# The clinical evaluation of *Basti* along with *Rasayana* on symptoms of post-COVID-19 syndrome: an open-labeled proof of concept pragmatic study—a study protocol

**DOI:** 10.1186/s40814-023-01322-1

**Published:** 2023-06-03

**Keywords:** Ayurved, *Basti*, COVID-19, Post-COVID-19, Pragmatic, *Rasayana*

## Abstract

**Background:**

Post-COVID-19 syndrome is a result of triggering various immune pathways and metabolic disturbances. *Basti* is an important per rectal Ayurveda-based treatment having multi-targeted actions. *Basti* and *Rasayana* treatment modulate immune responses by regulating pro-inflammatory cytokines, immune globulins, and functional properties of T cell. We propose to study the clinical evaluation of *Basti* along with *Rasayana* (rejuvenation therapy) on symptoms of post-COVID 19 syndrome.

**Methods and analysis:**

We designed a prospective, open-labeled proof of concept pragmatic study. The study duration is 18 months, and the intervention period are 35 days from the day of enrollment of the patients. The patients will be treated on the basis of Ayurvedic classification of *Santarpanottha* (over nutrition) symptoms and *Apatarpanottha (lack of nutrition)* symptoms. The *Santarpanottha* group will be treated within 3–5 days of oral *Guggulu Tiktak Kashayam* followed by 8 days of *Yog Basti* treatment and then 21 days of *Rasayana* therapy with *Brahma Rasayan*. The *Apatarpanottha* group will be treated within 3–5 days of oral *Laghumalini Vasant*, followed by 8 days of *Yog Basti* treatment and then 21 days of *Kalyanak Ghrit.*

The outcome measures of this study will be to evaluate the changes in fatigue severity scale, MMRC dyspnea chest pain scale, pain score assessed by VAS scale, smell and taste scale, WOMAC scale, Hamilton depression scale, Hamilton anxiety scale, Insomnia Severity Index, change in Cough Severity Index, facial aging scale, dizziness scale, Pittsburgh Sleep Severity Quality Index, functional status scale, and heart palpitation scale.

All adverse events will be monitored at each time throughout the study visit time. A total of 24 participants will be recruited to demonstrate with 95% confidence interval and 80% power.

**Discussion:**

Ayurveda treats *Santarpanottha* (originated from over nutrition) symptoms and *Apatarpanottha* (symptoms originated from undernutrition) symptoms differently; hence, inspite of the same disease or symptom management, changes depend upon the type of the origin. This pragmatic clinical study is developed on the fundamental grounds of Ayurveda.

**Ethics and dissemination:**

Ethics approval was obtained through the Institutional Ethics Committees of Government Ayurved College and Hospital on 23 July 2021.

**Trial registration:**

The trial is prospectively registered with the Clinical Trial Registry of India on 17 August 2021 [CTRI/2021/08/035732] after the Institutional Ethics Committee approval [GACN/PGS/Synopsis/800/2021 Date 23/7/2021].

**Supplementary Information:**

The online version contains supplementary material available at 10.1186/s40814-023-01322-1.

## Introduction

About 117 million people have been diagnosed with COVID-19 globally, with more than 2.6 million deaths till March 2021. It is caused by the novel severe acute respiratory syndrome coronavirus 2, i.e., SARS-CoV-2, in which heterogeneous virus manifests itself with a wide spectrum of symptoms, from asymptomatic to a life-threatening and fatal disease [1]. After COVID-19, some patients experience symptoms which are termed as a post-COVID-19 syndrome.

Post-COVID-19 syndrome can be seen in all those who had COVID-19, even if the illness was mild or with no symptoms. The commonly reported symptoms for post-COVID-19 syndrome are chronic fatigue, dyspnea, shortness of breath, chest pains, headache, loss of smell, loss of taste, and muscle and joint pain, followed by insomnia, depression, anxiety, itchy body, tachycardia, heart palpitations, tachycardia, anorexia, tingling fingertips, and brain fog [1]. A cytokine profile that is very specific is associated with several factors in the severe stage of this disease. It includes the induction of interferon production, interleukin (ILs), cytokine secretion, stimulation of granulocyte activation, and production of tumor necrosis factor (TNF). This causes intravascular hyperinflammation with changes in angiogenesis and coagulation in addition to the understanding of the immune response to COVID-19. Post-COVID-19 symptoms and their association with autoimmune diseases suggest that SARS-CoV-2 may trigger various diseases associated to the immune system and metabolism.

Viral infection leads to an aggressive immunological reaction on cardiopulmonary system, nervous system, hematological system, gastrointestinal tract, liver and kidney, and various other systems of the human body. SARS-CoV-2 infection can lead to destabilization of the liver that signals maximum alertness to whole organism and generates an increase in production of plasma biochemical markers of the tissue aggression in response to tissue-damaging agents [2]. Various complex molecular processes are responsible for post-COVID-19 syndrome, and targeting all of them at a time is a difficult task.

The gastro-intestinal tract is the largest immunological organ in the body, and its resident microbiota are known to modulate host responses. In post-COVID-19 syndrome, gut microbiota composition is disturbed and it is also associated with disease severity and plasma concentrations of several cytokines and inflammatory markers. The patients with COVID-19 report persistent symptoms after recovery and subsequently develop dysbiotic gut microbiota. There are various immune-related health problems post-COVID-19 [3].

COVID-19 is correlated with *Abhishangaj Jvara (fever* arising due external cause*)* in *Ayurveda* [4]*.* Some patients who suffered from COVID-19 followed *Langhana* (fasting) while some have not followed [5]. Therefore, currently observed signs and symptoms of post-COVID-19 syndrome can be categorized into two groups, i.e., *Santarpanottha* (excessive nutrition) and *Apatarpanottha* (poor nutrition) symptoms as per correlations with *Astang Hrdayam Sutrasthan* 14 [6]. COVID-19 epidemic can be termed as “*Janapadodhvans Vyadi* (epidemic)”*.* Charka described this concept of epidemic, which have a causing factor like polluted *Vayu* (air)*, Jala* (water)*, Desh* (country), and *Kaal* (time). *Panchakarma* (five cleansing process) and *Rasayana* (rejuvenation) therapy are two important treatments that are advised by Charka for various *Janapadodhvans Vyadi* [7, 8].

It is evident that COVID-19 leads to debilitation, and condition is more likely *Apatarpanothha*.

Recent articles have shown that post-COVID metabolic dysfunction can lead to insulin résistance and obesity. Recent researches have that there are metabolic clues that can lead to bidirectional pathologies.

Obesity, insulin resistance, development of obese type 2 DM may fall under *Santarpanottha*.

*Basti* (medicated enema) is one of the important *Panchkarma* used for many disorders; it has multitargeted action, hence many times, it forms an important part of the treatment, termed as “*Ardha Chikitsa”* [9]. Based on type of medicines used, *Basti* (medicated enema) can treat both *Santarpanottha* (excessive nutrition) as well as *Apatarpanottha* (poor nutrition) diseases. *Basti* (medicated enema) removes toxins, and it rejuvenates the body also. *Basti* is mentioned as a *Ardha Chikitsa* in classical ayurvedic texts, hence for broader purpose, we choose *Basti* [10]. *Vata* is an important Dosha that can show maximum number of *Nanatmaj Vyadhi* (various diseases), and it is also responsible for the movement of other *Doshas* [11]*.* *Basti* is an important treatment for *Vata dosha* [12]*.* Thatte et al. have shown that *Basti* modulates immune responses by regulating pro-inflammatory cytokines, immune globulins, and functional properties of T cell [13]. Rastogi et al. showed that *Rasayana* act as rejuvenation therapy, anti-stress, antioxidant, anti-inflammatory, anti-microbial, vaccine adjuvant, and confer immunity against various diseases [14]. We have decided to evaluate the efficacy of *Basti* and *Rasayana* on post-COVID-19 syndrome.

## Objectives

To evaluate the efficacy of Guggulutiktak Kashayam followed by *Yog Basti* (*Triphala Decoction Niruh Basti, medicated oil Anuvasan Basti*) followed by *Brahma Rasayana* on symptoms of *Santarpanottha* post-COVID-19 syndrome in the period of 35 days.To evaluate the efficacy of tablet Laghumalini Vasant followed by *Yog Basti* (*Brihatpanchmulsidhha Kshirbasti [medicated milk enema], Kshirbala tail [medicated oil* processed in milk*] Anuvasan Basti*) followed by *Kalyanak Ghrit* (medicated cow ghee) on symptoms *Apatarpanottha* post-COVID-19 syndrome in period of 35 days.

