**Assessments**						
Concomitant illness	×	×	×	×	×	×
Complete physical examination	×	×	×	×	×	×
Signs and symptoms assessment	×				×	×
Assessment of vitals	×	×	×	×	×	×
Ayurvedic evaluation	×	×	×	×	×	×
*Basti* charting				×		
Clinical scales assessment	×				×	×
Study drug dispensation		×	×	×	×	
compliance			×	×	×	×
Fatigue severity scale	×				×	×
MMRC dyspnea scale	×				×	×
Chest pain scale	×				×	×
VAS	×				×	×
Smell and taste scale	×				×	×
WOMAC Scale	×				×	×
Hamilton depression scale	×				×	×
Hamilton anxiety scale	×				×	×
Insomnia Severity Index	×				×	×
Cough Severity Index	×				×	×
Facial aging scale	×				×	×
Dizziness scale	×				×	×
Pittsburgh severity quality index	×				×	×
Functional status scale	×				×	×
Heart palpitation scale	×				×	×
Completion and outcome						×

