### Study design

This is a prospective, open-labeled proof of concept pragmatic study. The study duration is 18 months, and the intervention period is 35 days from the day of enrollment of the patients. The trial will be conducted at OPD, IPD of Kayachikitsa, Casualty and Periphery of Government Ayurved College and Hospital, Nagpur. Clinical assessment and Ayurveda-based clinical assessment will also be carried out. The detailed flow chart of process is shown in Fig. 1.

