### Eligibility

#### Inclusion criteria

The patients of either sex aged between 18 and 70 years are the ones included in the study, irrespective of caste, religion, socioeconomic, and educational status as long as they are willing to participate and have a history of positive RTPCR report under duration of > 21 days to 1 year. Those patients having > 20% (≥ 4) of symptoms will be included for the study and patients of post-COVID 19 syndrome who are willing to participate in the trial and are ready to give consent.

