### Trial intervention

An intervention will be decided on the basis of *Santarpanottha* symptoms or *Apatarpanottha* symptoms.

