### Clinical outcomes

#### Primary outcome

To evaluate the efficacy of Guggulutiktak Kashayam followed by *Yog Basti* (*Triphala Kwath Niruh Basti, Tiltail Anuvasan Basti*) followed by *Brahma Rasayana* on symptoms of *Santarpanottha* post-COVID-19 syndrome in the period of 35 days.To evaluate the efficacy of Laghumalini Vasant followed by *Yog Basti* (*Brihatpanchmulsidhha Kshirbasti, Kshirbala tail Anuvasan Basti*) followed by *Kalyanak Ghrit* on symptoms *Apatarpanottha* post-COVID-19 syndrome in the period of 35 days.

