### Statistical analysis

#### Sample size and power

The sample size for the study is calculated by using the formula with assumption which is made after the pilot study on 4 patients. The assumption made is that our treatment will reduce total symptoms by at least 40% with 95% confidence interval (*α* = 0.05) and 80% power of the study and expecting a dropout rate of 20%. Hence, a total of 24 patients will be recruited.

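### Objectives and primary outcome claim efficacy, but without a comparator the study can estimate only before-after change, in which natural recovery and some regression to the mean are mixed with any treatment effect

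*Protocol article*

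**What the plan says.** **Aim.** The Objectives open with "To evaluate the efficacy of Guggulutiktak Kashayam followed by" the rest of the first regimen, and give the second group a parallel objective. The Primary outcome section repeats both; its second half begins "To evaluate the efficacy of Laghumalini Vasant followed by" and names the second regimen. Sample size and power attributes the expected change to the intervention: "our treatment will reduce total symptoms by at least 40" percent.

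**Design.** Study design states: "This is a prospective, open-labeled proof of concept pragmatic study". Under Trial intervention, "An intervention will be decided on the basis of" symptom class. Both groups are headed as intervention arms, and no untreated, placebo or usual-care group is described.

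**Entry.** Inclusion criteria: "Those patients having > 20% (≥ 4) of symptoms will be included for the study". They also require a "history of positive RTPCR report under duration of" more than 21 days and up to 1 year.

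**Schedule.** In Table 1, eligibility is checked at Screening Day 0. The row "Signs and symptoms assessment" and the rows for all clinical scales are marked at Day 0, in Days 14 to 34 and at Day 35. None is marked at Day 1.

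**Analysis and limitations.** The Analysis section lists paired tests (Wilcoxon signed-rank, paired t) and between-group tests. The limitations section mentions the lack of funding and the restriction to clinical scales. It does not mention the missing control, natural recovery or regression to the mean.

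**The concern.** Efficacy is a statement about what the treatment adds to what would have happened anyway. With no comparator, nothing in the data shows what would have happened anyway.

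Two processes would lower symptoms without treatment. Patients may enter soon after infection, when continued recovery over the 35 days is plausible. They also enter because their symptom count reached a threshold, so a second count would tend to be lower on average even if nothing had changed. Because the qualifying visit supplies the only pre-treatment count, the second process cannot be separated out afterwards.

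At stake is the meaning of the headline result for both groups: a fall in symptoms would be a valid description of treated patients, but not evidence that the regimen caused it.

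**Working it through.** **1. Can any planned comparison isolate treatment?**
- Mann-Whitney and unpaired t tests compare the two groups. These differ both in patients (symptom class) and in regimen, so the tests cannot stand in for a control.
- Wilcoxon signed-rank and paired t tests estimate change within a group, which is treatment plus everything else that happens over 35 days.
- Each efficacy objective is set within one group, so it rests on the second kind.

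**2. Is the qualifying value the baseline?** The protocol does not call Day 0 the baseline, but Table 1 leaves no other pre-treatment symptom assessment. It also does not define the primary measure as a count; that reading follows from the entry rule and from the planned reduction in total symptoms.

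**3. The plan's own figure.** The total of 24 cannot be derived, because no formula, SD or comparison rate is given. Working backwards as a two-sided paired test on both groups pooled: 19 / 0.8 = 23.75, rounded up to 24. With n = 19, the standardised change detectable at 80% power is (1.96 + 0.84) / √19 = 0.64. A 40-point mean fall then implies an SD of 40 / 0.64, about 62 points. This SD is inferred, not stated.

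**4. Regression to the mean in the symptom count (all inputs assumed).** Source population normal with mean μ and SD 2.5; test-retest reliability r = 0.6 to 0.8; entry at 4 or more, taken as 3.5 with continuity correction. With a = (3.5 − μ)/2.5 and λ = φ(a)/(1 − Φ(a)), the mean at entry is m = μ + 2.5λ, and the expected fall with no treatment effect is (1 − r)(m − μ).

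| Source mean μ | Entry mean m | Fall, r = 0.8 | Fall, r = 0.6 |
|---|---|---|---|
| 2 | 5.04 | 12.1% | 24.1% |
| 4 | 5.69 | 5.9% | 11.9% |
| 5 | 6.15 | 3.7% | 7.5% |
| 6 | 6.72 | 2.1% | 4.3% |
| 7 | 7.41 | 1.1% | 2.2% |

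For example, with μ = 2 and r = 0.6: 0.4 × (5.04 − 2) / 5.04 = 24.1%. A separate simulation (19-item list, mean 3 to 6, SD 2, reliability 0.5 to 0.9) gave about 1% to 20% from regression to the mean alone.

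**5. Chance of a significant fall with no treatment effect.** Suppose symptoms improve by 15% or 20% untreated. Paired t test, two-sided 0.05, noncentrality (improvement / SD) × √n. The sizes are n = 19 (24 × 0.8 = 19.2, pooled) and n = 10 (12 × 0.8 = 9.6, one group if the split is even; the protocol fixes no split). The SD of percent change is 30 points (assumed) or 62 (from step 3).

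| Untreated improvement | SD | n = 10 | n = 19 |
|---|---|---|---|
| 15% | 30 | 29% | 54% |
| 20% | 30 | 47% | 78% |
| 15% | 62 | 10% | 17% |
| 20% | 62 | 15% | 27% |

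**The case against.** An uncontrolled study is a legitimate choice for an unfunded proof of concept within a postgraduate thesis, and the protocol uses that label openly. This stands: the absence of a control arm is not itself the error. The label does not, however, alter the objectives, the primary outcome or the sample-size assumption, all of which attribute the change to treatment.

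Four stronger readings are tempting, and the document does not support them.

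- *Regression to the mean is large.* Patients are recruited from people already presenting with post-COVID complaints, and 4 symptoms is only about a fifth of the list. If the source mean is 5 to 7, the fall is about 1% to 7.5%. The 24% end needs a mean of 2, where a normal distribution with SD 2.5 puts 21% of people below zero symptoms, which is impossible for a count.
- *Every outcome is measured from a selected baseline.* Direct selection applies to the symptom count. The 15 scales carry no entry threshold, so any effect on them is indirect.
- *A reduction far below 40% would be declared a success.* The Analysis section states neither a null hypothesis nor a success criterion, and planning on 40% while testing against no change is ordinary practice.
- *The study will credit recovery to treatment.* The objectives say evaluate; how the authors will conclude is not written down.

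**Conclusion.** The point holds in limited form. The efficacy wording goes beyond what the design can show: the data can support a statement about change under treatment in each group, and no statement about how much of that change is due to treatment.

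The size of the distortion cannot be computed from the protocol, which gives no SD, reliability or natural recovery rate. The ranges of roughly 1% to 24% for regression to the mean and about 10% to 78% for a significant result from untreated improvement show only that the answer depends on unstated inputs; neither is an estimate for this trial. If most patients lie well above 4 symptoms, or the count is reliable, natural recovery is the larger issue, and the conclusion is unchanged.

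This is a point that should be fixed, chiefly in the wording of the claim and the limitations. It does not require a different design.

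**What to change.** 1. Reword the objectives, primary outcome and planned conclusions as change from baseline under treatment, and state in the limitations that efficacy cannot be inferred without a control.
2. Repeat the symptom checklist at the existing Day 1 visit, before the first dose, and use it as baseline for the symptom count. This reduces short-term regression to the mean only. It does nothing about natural recovery or slower fluctuation, which is why item 1 is still needed.
3. Report the percent reduction in each group with its 95% CI beside the planned 40%, and describe change by time since the positive RT-PCR.

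The cost is wording, one short checklist of a few minutes per patient at a visit already scheduled, and a more modest conclusion. Sample size and treatment are untouched.

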## Methods and analysis

### Patient and public involvement

This study protocol is developed to evaluate the effect of *Basti* and *Rasayana* therapy to modulate immune responses in post-COVID-19 syndrome. Patients were not involved in the design, recruitment, or conduct of the study. The details of procedures with times are explained in Table 1.

**Table 1 Tab1:** Summary of activities

	Enrollment	Allocation	Post allocation			Completion
Timepoint	Screening Day 0	Day 1	Days 3 to 5	Days 5 to 13	Days 14 to 34	Day 35
**Enrollment**						
Eligibility criteria	×					
Informed consent	×					
Allocation		×				
**Interventions**						
Daily doses of drugs and *Basti* therapy						
**Assessments**						
Concomitant illness	×	×	×	×	×	×
Complete physical examination	×	×	×	×	×	×
Signs and symptoms assessment	×				×	×
Assessment of vitals	×	×	×	×	×	×
Ayurvedic evaluation	×	×	×	×	×	×
*Basti* charting				×		
Clinical scales assessment	×				×	×
Study drug dispensation		×	×	×	×	
compliance			×	×	×	×
Fatigue severity scale	×				×	×
MMRC dyspnea scale	×				×	×
Chest pain scale	×				×	×
VAS	×				×	×
Smell and taste scale	×				×	×
WOMAC Scale	×				×	×
Hamilton depression scale	×				×	×
Hamilton anxiety scale	×				×	×
Insomnia Severity Index	×				×	×
Cough Severity Index	×				×	×
Facial aging scale	×				×	×
Dizziness scale	×				×	×
Pittsburgh severity quality index	×				×	×
Functional status scale	×				×	×
Heart palpitation scale	×				×	×
Completion and outcome						×

### Study design

This is a prospective, open-labeled proof of concept pragmatic study. The study duration is 18 months, and the intervention period is 35 days from the day of enrollment of the patients. The trial will be conducted at OPD, IPD of Kayachikitsa, Casualty and Periphery of Government Ayurved College and Hospital, Nagpur. Clinical assessment and Ayurveda-based clinical assessment will also be carried out. The detailed flow chart of process is shown in Fig. 1.

**Fig. 1 Fig1:**
[figure not shown]
Flow chart of study

### Recruitment, screening, and consent

The participant of the age group 18–70 years will be selected for study. The study will include up to completion of 24 participants.

The investigator number 2 (PR) will be responsible for obtaining written informed consent from each participant prior to screening as per the national ethics guidelines [15]. An information sheet or case record format in a language best understood by the participant, giving details of the study, will be provided to the participant. Enough time will be given to the participant to make a voluntary decision to participate. The participant will be encouraged to ask questions and clear all doubts in a face-to-face interview with the investigator. After that, the participant will be asked to sign the consent form for the study research. The participants will be screened from the patients with post-COVID-19 syndrome complaints comprehensively by the study physicians for eligibility and to exclude any contraindication to participation in the study. If found eligible, the participants will be enrolled. The participants will be followed up at predetermined time endpoints (five visits including screening and completion visits) as per protocol till study completion (35th day). A detailed procedure is summarized in Fig. 1 and Table 1. Data will be recorded in case record form and will be then entered in an Excel sheet.

### Eligibility

#### Inclusion criteria

The patients of either sex aged between 18 and 70 years are the ones included in the study, irrespective of caste, religion, socioeconomic, and educational status as long as they are willing to participate and have a history of positive RTPCR report under duration of > 21 days to 1 year. Those patients having > 20% (≥ 4) of symptoms will be included for the study and patients of post-COVID 19 syndrome who are willing to participate in the trial and are ready to give consent.

